### Outcome Measures

The primary outcome is functional status measured over 12 weeks. Functional status will be measured using modified Barthel index (MBI), a 100-point ordinal scale for the assessment of a patient’s functional state. The MBI assesses activities of daily living over 10 domains comprising transfers, ambulation, stair climbing, bathing, dressing, toileting, bowel control, bladder control, personal hygiene, and feeding [29].

Secondary outcomes include physical performance, quality of life, length of stay in CH, 30-day readmission rates, and cost-effectiveness over 12 weeks. Patients who are admitted under RDG total knee replacement will have an additional outcome measure of joint range. The outcome measures as well as the method of measurement are listed in Table 3. Health care cost will be calculated from electronic medical records and supplemented with survey data regarding the number of DRC or home therapy sessions attended, manpower hours to train patients to use Rebee, costs of Rebee software and hardware, and use of outpatient community services (eg, day care center, home nursing, housekeeping, and meals on wheels). The tools to be used in this study to measure the outcomes are validated and implemented in routine clinical care.

**Table 3 table3:** Primary and secondary outcome measures.

Variables			Data source, method of measurement, and definitions		Time points
Primary outcome					
	Functional status	Survey: MBI^a^. To establish the degree of independence from any help. A score from 0- 100 using the MBI questionnaire, with 100 being fully ambulant without any help.		Baseline and 4, 8, and 12 weeks	
Secondary outcomes					
	Joint range	Measurement using goniometer on affected knee. Active and passive range of motion (flexion and extension) of affected knee.		Baseline and 4, 8, and 12 weeks	
	Physical performance	Measured by performing 5CST^b^. Measures the time taken to complete 5 sit to stands (in seconds)		Baseline and 4, 8, and 12 weeks	
	Quality of Life	Survey: EQ-5D-5L		Baseline and 4, 8, and 12 weeks	
	Length of stay	Electronic medical records		Date of discharge from CH^c^ minus date of randomization	
	30-day readmission rates	Electronic medical records		12 weeks	
	Direct health care cost	Electronic medical records: cost of inpatient stay		12 weeks	
	Direct health care cost	CRC’s^d^ daily expenditure of manpower		4, 8, and 12 weeks	
	Direct health care cost	Rebee costs: software and hardware		12 weeks	

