### Sample Size

We calculated the sample size based on the primary outcome of MBI scores, which is evaluated at recruitment and at 4, 8, and 12 weeks. The historical mean of the MBI is 73 (SD 25). The study aims to detect a difference of 5 points between the control and intervention groups assuming a correlation of 0.35 between the repeated measurements. The sample size estimated to detect this difference with 80% power and a 5% significance level is 175 participants per group assuming equal allocation between arms. After accounting for 20% attrition, the total sample size required for the study is 450.

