### Statistical Analyses

Participants will be analyzed via an intention-to-treat approach. Participant characteristics will be summarized using median (IQR) or mean (SD) for nonnormally distributed and normally distributed data, respectively, and count and percentage for categorical variables.

Linear mixed-effects model will be used to assess the pattern of change in the primary outcome of the MBI score and secondary outcomes of EQ-5D, 5-time chair stand test (5CST), and joint range over the 12-week follow-up period. A uniform correlation structure will be specified to model the within-subject correlation of these repeated measures. MBI, EQ-5D, 5CST, and joint range of motion will be treated as continuous outcomes. Normality of continuous outcome variables will be assessed through visual inspection methods. If normality assumptions are met, parametric methods will be used; otherwise, a suitable transformation may be performed to address the issue of nonnormality.

As individuals of different age groups have varying body composition, functional capacity, and physiological reserves, there may be differential influences on baseline functional ability and recovery trajectories. To ensure that any potential age-related differences are accounted for, we will first assess the interaction between the age category, treatment groups, and duration of time. We will stratify into age categories, and if statistically meaningful effect modification by age is observed, an age-stratified analysis will then be conducted.

Poisson regression will be used to compare length of stay between intervention and control groups. If there is evidence of overdispersion and/or zero inflation, negative binomial regression or corresponding zero-inflated models will be implemented instead.

Key prognostic factors such as baseline MBI, RDG grouping, and time will be adjusted a priori. The secondary outcome based on 30-day readmission will be compared between the intervention and control group using modified Poisson regression. The effect estimate will be quantified in terms of relative risk and its 95% CI.

For both the primary and secondary outcomes, linear mixed-effects model on the log-transformed scale will be applied if the model assumptions are violated.

Missing data are expected due to the nature of the study and will be handled by imputation.

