The preferred method of imputation will be applied accordingly based on the degree of missingness, such as last observation carried forward.

The cost-effective analysis will evaluate both direct cost savings and cost-effectiveness in terms of quality-adjusted life years (QALYs). To assess direct cost savings, the analysis will evaluate the difference in length of stay at the hospital between the intervention and control group (Table 4). The results will be expressed as mean cost differences between groups. Cost per QALY gained will be evaluated for the cost-effectiveness of the intervention. QALY will be derived using EQ-5D-5L utility scores, and incremental cost-effectiveness ratios (ICERs) will be calculated. The ICERs will be compared to established willingness-to-pay thresholds to determine the cost-effectiveness of the intervention. Sensitivity analyses will be performed to account for uncertainties in cost and QALY estimates. Results will be presented using cost-effectiveness planes and acceptability curve.

**Table 4 table4:** Cost-accounting for the cost-effectiveness analysisa.

Cost category	Cost type	Cost item	Unit of measurement	Source of unit cost	Applicable to
Hardware	Direct	Rebee kits	Per kit per day	Research collaboration agreement	Intervention
Software	Direct	Rebee subscription	Per patient per day	Research collaboration agreement	Intervention
Inpatient care	Direct	Average length of stay	Per patient per day	Electronic medical records	Control and intervention
Manpower	Direct	CRC’s^b^ daily EOM^c^	Per day	Human resource	Intervention

^a^The statistical analysis will be conducted using R (R Foundation for Statistical Computing). All evaluations will be made using 2-side *P* values at the 5% level of significance.

^b^CRC: clinical research coordinator.

^c^EOM: expenditure of manpower.

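### The 5-time chair stand test has a value only for patients who complete five stands; with no score for inability, the plan as written tends to shrink a real benefit on this secondary outcome

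*Protocol article*

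**What the plan says.** Outcome Measures, Table 3, takes the 5CST at baseline and at 4, 8 and 12 weeks and gives one definition: "Measures the time taken to complete 5 sit to stands (in seconds". No score, cap or category is given for a patient who tries and cannot finish.

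Statistical Analyses puts the test on a continuous scale: "MBI, EQ-5D, 5CST, and joint range of motion will be treated as continuous outcomes". A linear mixed-effects model is used for the "secondary outcomes of EQ-5D, 5-time chair stand test (5CST), and joint range over the 12-week follow-up period". If assumptions fail, a "linear mixed-effects model on the log-transformed scale will be applied if the model assumptions are violated".

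One missing-data rule covers every outcome: "Missing data are expected due to the nature of the study and will be handled by imputation". The method is left open: "The preferred method of imputation will be applied accordingly based on the degree of missingness, such as last observation carried forward".

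On the population, Sample Size states: "The historical mean of the MBI is 73 (SD 25". Eligibility Criteria excludes patients who cannot fully weight bear and requires that patients can do the Rebee exercises. It does not require rising from a chair.

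**The concern.** In a timed test, failing to finish is the worst result. On a scale of seconds it has no number, and a log transformation does not supply one. Choosing an imputation method by the amount of missing data takes no account of why a value is absent. Carrying the last value forward credits a patient who has lost the ability with an earlier, better time, and it has nothing to carry for a patient unable at baseline.

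If the programme helps, fewer intervention patients are unable. That arm then contributes more slow times, while the control arm loses more of its worst patients. The comparison is no longer between the randomised groups, and the difference in seconds is pulled towards zero.

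Non-completion is plausible here. Patients are inpatients aged up to 99 with hip fracture, musculoskeletal conditions or deconditioning. The Table 1 inpatient exercises are all done lying or seated, and the first 5CST is taken at baseline.

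The test is secondary, but it carries weight. The trial is unblinded, the MBI and EQ-5D-5L are surveys, and Strengths and Limitations accepts that intervention participants may report more favourably. Joint range is measured only after total knee replacement. The 5CST is therefore the only performance-based measure taken in all patients.

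**Working it through.** **1. The plan's own figure.** The article gives no 5CST figure; its sample size rests on the MBI. With a difference of 5, SD 25, two-sided 5% and 80% power, one time point needs 2 × [25 × (1.960 + 0.842) / 5]² = 392.4, so 393 per group. With one baseline and three follow-up values at correlation 0.35, the covariance-adjusted factor is (1 + 2 × 0.35)/3 − 0.35² = 0.444. Then 392.4 × 0.444 = 174.3, so 175 per group, as stated. For attrition, 350/0.8 = 437.5, so 438; the article's 450 is close. None of this involves the 5CST.

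**2. What happens to a failed attempt.** Set side by side, the passages give a scale defined only for completers, a model that needs a number, a fallback that needs a number, and a generic imputation rule. Nothing assigns a value to inability. Nothing says that a failed test is coded as missing either; that follows only if no other document scores it.

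**3. Shrinkage.** All inputs are assumptions. Underlying time is log-normal with baseline median 22 s and log-SD 0.5. The baseline to follow-up correlation is 0.5, controls improve by 0.2 on the log scale, and the intervention adds a uniform 0.2. Patients whose underlying time exceeds a limit T cannot complete.

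For each arm at follow-up, m is the log median, s = 0.5, a = (ln T − m)/s, and Φ is the normal distribution function:
- all patients: exp(m + s²/2)
- completers only: exp(m + s²/2) × Φ(a − s)/Φ(a)

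The control median is 22 × e^−0.2 = 18.0 s, so the control mean is 20.4 s. The intervention mean is 20.4 × e^−0.2 = 16.7 s. The full difference is −3.7 s. The carried-forward column comes from simulation with 400,000 patients per arm, and the completers column agrees with that simulation.

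| T (s) | Controls unable at follow-up | Completers only | Carried forward | Share lost |
|---|---|---|---|---|
| 25 | 26% | −1.5 s | −1.7 s | 59%, 55% |
| 30 | 15% | −2.0 s | −2.1 s | 47%, 43% |
| 40 | 5.5% | −2.7 s | −2.8 s | 27%, 23% |
| 60 | 0.8% | −3.4 s | −3.5 s | 8%, 6% |

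Carrying forward is slightly better than dropping the patient, but it does not repair the loss. Scoring non-completers at T gives −2.4, −2.8, −3.3 and −3.6 s, which recovers part of it.

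On the log scale the completers' mean is m − s × φ(a)/Φ(a), with φ the normal density. The difference becomes −0.117, −0.139, −0.169 and −0.193 against −0.20, a loss of 41%, 31%, 16% and 4%. The fallback reduces the problem without removing it.

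If the benefit is confined to patients near or beyond the limit at baseline, the proportionate loss is larger. At T = 40 the full difference is −1.37 s and completers show −0.69 s, a loss of 50%. No simulated scenario changed sign.

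**4. Can the sign change?** Let always-able patients take 18 s under control and 17 s under the intervention. Let a share pC be unable under control and pI under the intervention, with rescued patients taking r seconds. The observed difference is [(1 − pC) × 17 + (pC − pI) × r]/(1 − pI) − 18.
- 30% v 20%, r = 40: (11.9 + 4.0)/0.80 − 18 = +1.9 s
- 20% v 10%, r = 30: (13.6 + 3.0)/0.90 − 18 = +0.4 s
- 15% v 10%, r = 35: (14.45 + 1.75)/0.90 − 18 = 0.0 s
- 10% v 8%, r = 35: (15.3 + 0.7)/0.92 − 18 = −0.6 s
- 5% v 4%, r = 30: (16.15 + 0.30)/0.96 − 18 = −0.9 s

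The sign changes when (pC − pI) × (r − 18) exceeds (1 − pC) × 1 s. With these inputs that takes about 10 percentage points of patients moving from unable to slow.

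**The case against.** The strongest objection is that this is inferred from silence. No sentence classes a failed attempt as missing. Scoring of failed attempts often sits in an analysis plan, a case report form or an assessor manual, none of which is shown. Outcome Measures says the tools are validated and in routine use, so a scoring convention may exist. A reader might infer that the article prescribes imputing inability as ordinary missing data, or that carrying forward is fixed. It does neither: the wording is "such as last observation carried forward", an example. What remains is that the article does commit to a scale, a model, a fallback and a way of choosing the imputation method, and none of these gives inability a value.

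A reader might also infer that a real benefit would be shown as harm. The documents do not support this. It appears only in arithmetic with a large arm difference in inability, or with no benefit at all among patients who could already stand.

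The size is also open to challenge. Excluding patients who cannot fully weight bear lowers the number affected, and the article gives no rate. The 26% row implies about 40% unable at baseline, since ln(25/22)/0.5 = 0.256 leaves 39.9% above the limit; nothing in the article supports so high a rate. Nor do the calculations fit the planned mixed model with its baseline MBI and diagnostic-group adjustment. Both points stand, so the percentages are illustrations rather than forecasts.

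**Conclusion.** The point holds as a conditional one. As the article stands, a patient who cannot complete five stands has no 5CST value, and the stated approach would drop that patient or supply a time that conceals the failure. If no other document scores inability, the estimated benefit tends to be too small. Shrinkage is the robust result. It is minor at about 1% unable, about a quarter at 5.5%, and over half only at rates near 26%. These figures assume a log-normal underlying time and a uniform benefit; a benefit concentrated in frailer patients would lose proportionately more. A sign change is a remote possibility that needs a large shift from unable to slow. The consequence is confined to one secondary outcome, though it is the one performance-based measure available in every patient. If an existing scoring rule treats inability as the worst result, stating it settles the matter.

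**What to change.** Set the rule before any comparison by arm is seen; the article reports data collection complete and analysis under way.

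- Score an attempted but failed 5CST as the worst outcome. Options are a worst rank, a capped value, or a rate of 5 divided by seconds with 0 for inability. The rate cannot be combined with the log fallback, because zero has no logarithm.
- Do not carry a time forward over a failed test.
- Limit imputation to tests not done for reasons unrelated to ability.
- Report the number unable by arm and visit.

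The cost is a change of wording and a recoding step, with no new visits. There are three downsides. The effect is no longer in plain seconds, so completers' times should also be shown descriptively. Scores pile up at zero or at the worst value, which fits a Gaussian model poorly, so a rank-based or robust check is needed. And the change is possible only if existing records separate unable from not done. If they do not, the article should say so and interpret the 5CST result with that limitation.

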The primary aim of this RCT is to determine if the addition of ATLAS to usual care improves functional status, as compared to usual care alone, in patients admitted to CHs for rehabilitation for hip fracture, musculoskeletal conditions, or deconditioning. The secondary aim is to determine if this also affects patients’ quality of life, length of stay in CHs, 30-day readmission rates, and clinical cost-effectiveness, as compared to usual care alone. The hypothesis is that the addition of ATLAS to usual care improves functional status and quality of life, reduces length of stay in CHs and 30-day readmission rates, and increases clinical cost-effectiveness, as compared to usual care alone. The findings from this study may provide evidence for an enhanced, cost-effective, and sustainable care model for patients admitted for rehabilitation to a CH.

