### Strengths and Limitations

This trial will contribute in several ways to existing knowledge and research regarding telerehabilitation devices and rehabilitation programs. First, it will test user acceptability and compliance with telerehabilitation devices and systems to guide the practicability of application of such devices to routine clinical practice. Second, this will evaluate the cost-effectiveness of such systems versus usual care alone to provide an economic evaluation encompassing resource use, patient-reported quality of life, and physical function improvement. Finally, this will also test whether the addition of such a telerehabilitation system as compared to usual care alone will improve outcomes in terms of functional improvement, length of stay in a CH, and 30-day readmission rates.

There are some limitations to this study. First, it was not possible to blind participants as the intervention involves receiving a physical Rebee device as well as physical sessions to teach the participant about the use of the Rebee device. This might change the behavior and response of participants in the intervention group, causing them to provide more positive outcomes. The difficulty in blinding participants may also increase patient dropout in the control arm as they do not perceive any immediate benefits to them being in the study. Second, the total health care costs calculated in the cost-effectiveness analysis may be underestimated due to omission of certain costings such as postdischarge service use costs and unplanned readmission costs. These costs were excluded because the data on postdischarge service use were collected through patient self-report and could not be verified. On the other hand, there is insufficient information on readmission costs. To minimize inaccuracy, it was decided that these costings will be excluded from the cost-effectiveness analysis. Another limitation is the language barrier, as the Rebee application is only available in English and Mandarin. Considering that Singapore is a multiracial country, this may deter participants who can only read Malay or Tamil from participating in this study. Finally, there is also a potential confounder, which is the digital literacy of participants, which was not assessed in this study. To address this issue, the study team will provide support to participants and caregivers, ensuring that they are able to operate Rebee independently.

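### Length of stay does not distinguish how the stay ended, so a return to acute care is recorded as a short stay and a cost saving

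*Protocol article*

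**What the plan says.** In the Protocol article, Table 3 (Outcome Measures) takes length of stay from electronic medical records and defines it as "Date of discharge from CH^c^ minus date of randomization".

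Statistical Analyses fixes the population, "Participants will be analyzed via an intention-to-treat approach", and the model: "Poisson regression will be used to compare length of stay between intervention and control groups". The stated fallbacks are negative binomial and zero-inflated models, for overdispersion or excess zeros.

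The Introduction hypothesises that adding ATLAS "reduces length of stay in CHs and 30-day readmission rates". The economic part of Statistical Analyses says: "To assess direct cost savings, the analysis will evaluate the difference in length of stay at the hospital between the intervention and control group". Inpatient care is costed per patient per day in Table 4.

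Strengths and Limitations says that total costs may be underestimated because of the "omission of certain costings such as postdischarge service use costs and unplanned readmission costs", and explains that "there is insufficient information on readmission costs".

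**The concern.** The definition counts days until the patient leaves the CH and does not ask why the patient left. A patient who returns to acute care after a week and a patient who goes home fit after a week have the same value. The hypothesis treats that value as favourable for both.

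The economic analysis then converts the difference in days into money. The CH days cut off by a transfer lower the measured cost, and the acute stay that replaces them does not appear among the cost items. An arm with more transfers could seem to shorten stay and save money, and an arm that prevented transfers could seem worse on both. The limitations text concedes that costs may be too low overall, but not that the difference between arms could be affected.

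Transfers are foreseeable here. Patients up to age 99 come from acute hospitals, readmission is itself an outcome, and hospital admission is listed among the reasons for stopping the device.

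**Working it through.** **Reading the rule.** Table 3 gives one formula. The intention-to-treat statement exempts nobody, and the model fallbacks concern the shape of the distribution, not the way a stay ended. For a transfer to acute care, the date of leaving the CH is the natural discharge date, so the recorded stay is short. For a death this follows only if the record enters the date of death as the discharge date. Otherwise the stay is undefined and would fall under the general imputation rule. A temporary transfer followed by return to the CH is also not covered.

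**Plan's own figure.** There is none for length of stay. The sample size (175 per group) was calculated for the MBI and is used below only as a group size.

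**Inputs.**
- *L*, stay ending in discharge home: 21 to 28 days, from the 3 to 4 weeks given under Usual Care. The outcome counts from randomisation, so if patients are randomised some days after admission, the true *L* is lower and so is the shift.
- *t*, stay ending in transfer or death: 7 to 10 days (assumed).
- *p*, share of patients whose stay ends that way: not in the documents; assumed values of 5% to 20% per arm.

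**Formula.** Mean recorded stay = (1 − *p*)·*L* + *p*·*t*. If *L* and *t* are the same in both arms, the difference (intervention minus control) is −(*p*₁ − *p*₀)·(*L* − *t*).

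**Results, with no true difference in time to going home.**

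| Control *p*₀ | Intervention *p*₁ | Shift in mean stay (days) |
|---|---|---|
| equal | equal | 0 |
| 5% | 10% | −0.05 × (11 to 21) = −0.55 to −1.05 |
| 10% | 5% | +0.55 to +1.05 |
| 5% | 15% | −0.10 × (11 to 21) = −1.1 to −2.1 |

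As a ratio of means, 5% against 10% gives 0.96 to 0.97.

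**Effect on the test.** Assume an SD of stay of 10 days, 175 per arm, *L* = 21 and *t* = 7. The standard error is 10·√(2/175) = 1.07 days.
- 12% against 8%: 0.04 × 14 = 0.56 days, or 0.52 standard errors. The two-sided rejection probability is 8.2%.
- 15% against 5%: 0.10 × 14 = 1.4 days, or 1.31 standard errors. The rejection probability is 25.8%.

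With about 203 per arm (407 recruited), the standard error is 0.99 and the probabilities are about 9% and 29%.

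**Effect on cost.** The apparent saving per patient is the shift in days times the per-day CH cost, which the documents do not give. Table 4 has no line for acute-hospital days. Table 3 lists the cost of inpatient stay from the records over 12 weeks, which could be read more widely, but Table 4 and the stated exclusion of readmission costs narrow it.

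**The case against.** No passage mentions death or acute transfer in connection with length of stay. Study Setting and Usual Care use discharge for going home or back to the community, so discharge in Table 3 may mean the same, leaving transfers unspecified. This stands in part. It makes the point conditional for death, and it is a reason to ask for the term to be defined. It does not remove the point for transfers, because the formula carries no restriction on destination.

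Handling of such events is often left to the SAP, which is not shown. But the article fixes the definition, the model with its fallbacks, the link to savings and the exclusion of readmission costs. A SAP would have to add to or depart from these to remove the problem.

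Bias between arms needs rates that differ by arm. The intervention is described as minimal risk, and no rates are given. This stands in full. A gap as wide as 15% against 5% would itself be a safety signal that the monthly adverse event checks could reveal. The rejection probabilities above are therefore not false-positive rates for an inert intervention; they presuppose a real difference in transfer or death.

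Finally, CH days actually used are a legitimate measure of resource use, and a transferred patient did use fewer. This also stands. The fault in the cost comparison is the missing acute days, not the counting of CH days. In the cost-per-QALY analysis, QALYs lost through death would partly offset the apparent saving.

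**Conclusion.** The point holds for acute transfer, and for death on condition that the record's discharge date is the date of death. As written, such stays are short, read as favourable and read as cheaper, with no offsetting acute cost.

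On the assumed stays, each 5-point difference between arms in these events moves mean stay by roughly 0.5 to 1 day, in either direction. Equal rates give no distortion. The size rests on assumed rates and timings, not on protocol figures.

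A reader might infer that the plan scores deaths as successes, or that the stay result will be biased in favour of ATLAS. The documents support neither: death is not mentioned in this context, and nothing indicates that the rates will differ or in which direction. The matter concerns a secondary outcome and the cost-saving analysis; the primary MBI analysis is unaffected. It should be corrected, but does not threaten the trial's main conclusion.

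**What to change.** - Keep mean CH days, with the planned count model, as the measure of resource use.
- Rest any claim of faster recovery on time from randomisation to live discharge to the community, with death and acute transfer as competing events (cause-specific or Fine-Gray), or on days alive and out of any hospital to week 12.
- State what discharge covers, including a temporary transfer with return, and report discharge destination by arm.
- In the cost-saving analysis, add acute-hospital days after transfer, taken from the electronic records and costed at a per-day rate varied in sensitivity analysis. Do not disallow CH days that were not used.

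The cost is modest: analysis-plan wording, extraction of discharge destination and acute-stay dates (destination is not listed as a collected item, so availability must be confirmed), and a main estimate less direct to read than a ratio of mean days. Data collection is complete and analysis is under way, so the change should be fixed before arms are compared, or labelled post hoc if they already have been.
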